### Safety monitoring committees

The TMG and the DMC are independent of each other. The function of the DMC is delineated in the DMC charter (online supplementary file 2). The chief investigator of the trial will report to the DMC on the course of the trial during open sessions of the DMC. All DMC meetings will be held in private without any involvement of the trial team. The unblinded statistician is the only person who reports to the DMC and is part of the TMG. However, any data presented to the TMG are presented in a manner that maintains the blind.

The TMG will assess safety in a blinded manner on an ongoing basis at regular intervals during the course of the trial. Between part A and part B, the DMC will be formally convened to review the unblinded data with the unblinded statistician to determine whether it is reasonable for the trial to progress to the next stage.

### Statistical methods and data handling

This is an exploratory study that is not designed to formally test a hypothesis in a confirmatory fashion. Given that both parts of the trial have clinical safety as primary endpoints, a formal power calculation is not relevant. A sample size of 57 patients is achievable within the proposed time scale, given the size of the targeted patient population at our study site. The frequency of AEs per patient will be summarised for each event based on dose level. Summary statistics of laboratory values by dose and visit will be produced where required. The statistician will use the data from each group to perform a modelling analysis of the effect of aldesleukin based on dose and effect size using a smoothed line plot of the mean and 95% CIs. Generally summary statistics of continuous variables will report mean, median, SD, min and max, although a log-transformed scale may be used where the data are skewed. Binary or categorical variables will be summarised using the p% (x/n) format. The Treg data and other secondary biomarker endpoints will be summarised with individual patient profiles over time, and summary statistics will be broken down by dose and visit. Formal estimates of the differences between doses will be made at each time point with accompanying 95% CIs and p values.

Subjects will be coded by a numeric code to create an anonymous dataset. All data will be transferred into a case report form, which will be coded onto a MACRO database. All data will be anonymised and stored encrypted on a secured computer to ensure patient confidentiality.

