**Method and analysis:**

Low-dose interleukin-2 in patients with stable ischaemic heart disease and acute coronary syndromes is a single-centre, first-in-class, dose-escalation, two-part clinical trial. Patients with stable IHD (part A) and ACS (part B) will be randomised to receive either IL-2 (aldesleukin; dose range 0.3–3×10^6^ IU) or placebo once daily, given subcutaneously, for five consecutive days. Part A will have five dose levels with five patients in each group. Group 1 will receive a dose of 0.3×10^6^ IU, while the dose for the remaining four groups will be determined on completion of the preceding group. Part B will have four dose levels with eight patients in each group. The dose of the first group will be based on part A. Doses for each of the subsequent three groups will similarly be determined after completion of the previous group. The primary endpoint is safety and tolerability of aldesleukin and to determine the dose that increases mean circulating Treg levels by at least 75%.

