## Background

Despite major advances in the treatment, ischaemic heart disease (IHD) remains a significant cause of mortality and morbidity. It is now firmly established that inflammation and the immune response are crucial to the pathophysiology of IHD. This is true both in atherosclerosis, which underlies stable angina, and in progression to plaque instability and disruption in acute coronary syndrome (ACS).^1^

Although the innate immune system has been better studied in atherosclerosis, the role of the adaptive immune responses is now being increasingly understood. Several studies reported a perturbation of the T cell repertoire in ACS patients^2^ with expansion of an effector and activated T cell subset^3^ which is, at least in part, directed to antigens contained in the disrupted plaque.^4^ Initial preclinical findings have shown that regulatory T (Treg) cell-mediated immunity reduces experimental atherosclerosis and plaque inflammation.^5^

Even though Treg cells in humans are less distinct and more heterogeneous than in mice,^6^ there is evidence to demonstrate their role in IHD. In patients with ACS, there is an imbalance between T effector and Treg cells. Despite the effector T cell compartment activation, the percentage and function of circulating Tregs appear to be significantly decreased in in the setting of ACS.^7–10^ This imbalance is thought to play a key role in coronary plaque progression and destabilisation. In this context, low levels of circulating baseline CD4^+^Foxp3^+^ Treg cells were associated with an increased risk for acute coronary events in the Malmö Diet and Cancer Study.^11^

Following myocardial infarction, the ischaemic and necrotic myocardial tissue may present self-antigens to the immune system, leading to antigen-specific, autoimmune adaptive responses.^12 13^ Recent studies indicate that CD4^+^ T cells, and particularly Treg cells, are important for the control of postischaemic immune responses and the promotion of myocardial healing.^13–16^ In another study, inhibition of Treg recruitment to the site of myocardial injury resulted in excessive postischaemic inflammation, matrix degradation and adverse remodelling.^14^ In contrast, in vivo expansion of Treg cells or their therapeutic activation by superagonistic anti-CD28 antibodies attenuated left ventricular remodelling and improved cardiac function.^15 16^

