**Figure 1 F1:**
[figure not shown]
Trial design per patient. Each patient will make a total of eight study visits. IL-2, interleukin; V, visit.

There are two follow-up visits (V7 and V8). Assessments during both visits will include a medical review, physical examination, vitals, ECGs and safety bloods tests. Additionally, at V8, a follow-up thyroid function blood test and echocardiogram will be performed.

In addition, during visits V2 and V7 (figure 1), cardiac biomarkers (high sensitivity C reactive protein (hs-CRP), IL-6, brain-type natriuretic peptide (BNP) and troponin) and lymphocyte subsets (including Treg level, see below) analysis will be performed. During visit V8, cardiac biomarkers will be reaassessed.

A total of 25 patients, five in each of the five dosing groups, will be included in part A (drug:placebo ratio of 3:2). In line with current phase I trial designs, a sentinel dosing approach will be employed whereby the first two patients of each group will be allocated to either aldesleukin or placebo in a random order. After a blinded safety review of these first two patients, the remaining patients will then be dosed (see figure 2).

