#### Part B

As with part A, the primary endpoint will be safety and tolerability of IL-2. A further primary endpoint will be the change in mean circulating Treg levels and whether IL-2 increases mean circulating Treg levels by at least 75% over the 5 days of the treatment period. Exploratory endpoints are the same as for Part A.

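### The part B 75% Treg target names no comparator, and the only formal comparison stated (dose differences at each time point) does not estimate it

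*Protocol article*

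**What the plan says.** - **Endpoint.** Outcome measure, Part B, makes Treg primary beside safety: "A further primary endpoint will be the change in mean circulating Treg levels". The threshold is set in the same sentence, as the question "whether IL-2 increases mean circulating Treg levels by at least 75% over the 5 days of the treatment period". The abstract puts the aim as "to determine the dose that increases mean circulating Treg levels by at least 75" per cent. None of these names a comparator. In part A, Treg is exploratory.
- **Analysis.** Under Statistical methods and data handling, the Treg data "will be summarised with individual patient profiles over time, and summary statistics will be broken down by dose and visit". The formal comparison is: "Formal estimates of the differences between doses will be made at each time point with accompanying 95% CIs and p values". A smoothed plot of dose against effect size with 95% CIs is also planned, but effect size is not defined. Placebo is not mentioned in that section. For continuous variables in general, the mean and median are reported, "although a log-transformed scale may be used where the data are skewed".
- **Status.** The same section groups Treg with the secondary biomarker endpoints, although Outcome measure, Part B makes it primary.
- **Sampling.** Study protocol, Part A: "during visits V2 and V7 (figure 1), cardiac biomarkers" and lymphocyte subsets, including Treg, are analysed. Part B follows the same visits.
- **Design.** The trial is randomised, double-blind and placebo-controlled. Part B has four groups of eight, allocated 6:2.
- **Setting.** Background: "circulating Tregs appear to be significantly decreased in in the setting of ACS". Part B patients must be willing to be dosed within 8 days of admission.

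**The concern.** A primary endpoint with a numerical threshold needs a stated reference, and the stated analysis should estimate the quantity that is compared with the threshold. Here the target is a percentage rise, while the formal comparison is between doses at a visit. A difference between two doses cannot show whether either of them reaches 75%.

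The choice of reference matters more in part B than in a stable population. V2 falls soon after an acute event in which the article says Tregs are reduced, so Treg could change by V7 without drug. If the target is then read from active patients alone, that change is counted towards the 75%.

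The Treg results in ACS are meant to help choose the dose for later trials, so a misread threshold would carry forward. The placebo patients and V2 samples that would settle the question are already being collected.

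**Working it through.** **1. Numbers of patients.** Part A: 5 × 5 = 25. Part B: 4 × 8 = 32. Total 57, which reproduces the stated sample size. Part B has 4 × 6 = 24 active and 4 × 2 = 8 placebo patients. The article gives no SD or power for Treg, so there is no precision figure to reproduce.

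**2. What the stated comparison estimates.**
- *At V2.* Assuming the sample precedes the first dose (the text does not give the time within the visit), a difference between doses reflects chance or differences between successively enrolled groups. It cannot reflect treatment.
- *At V7.* A difference between doses compares levels. Groups are enrolled one after another, so it also carries any V2 difference between them. If placebo counts as a dose, the V7 contrast with placebo is a fair comparison, but it is unadjusted for V2 and, on the raw scale, is not a percentage.

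**3. Effect of the reference.** If active patients rise 75% from V2 and placebo rises by r (assumed), the drug effect is 1.75/(1 + r) − 1.

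| Assumed placebo rise r | Drug effect behind a raw 75% |
|---|---|
| 0% | 75% |
| 10% | 1.75/1.10 − 1 = 59% |
| 20% | 1.75/1.20 − 1 = 46% |
| 40% | 1.75/1.40 − 1 = 25% |

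**4. Chance of reaching 75% when the drug effect is smaller.** Assume a true drug effect of 45%, an SD of log change of 0.35, six active patients and eight pooled placebo patients.
- Raw reading, placebo +20%: z = (ln 1.75 − ln 1.74)/(0.35/√6) = 0.04, probability 48%.
- Raw reading, placebo flat: z = (ln 1.75 − ln 1.45)/(0.35/√6) = 1.32, probability 9%.
- Placebo-adjusted, in either case: z = (ln 1.75 − ln 1.45)/(0.35 × √(1/6 + 1/8)) = 0.99, probability 16%.

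The 48% arises because 1.20 × 1.45 = 1.74 lies almost on the threshold. With flat placebo the adjusted estimate crosses wrongly more often than the raw one, because it also carries the placebo patients' variability.

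**5. Precision.** The 95% CI half-width, in SDs of log change, is t(0.975, df) × √(1/n₁ + 1/n₂).
- Six against the two placebo patients of the same group, df 6: 2.447 × 0.816 = 2.00.
- Six against two, with variance pooled over part B, df 32 − 5 = 27: 2.052 × 0.816 = 1.68.
- Six against eight pooled, df 27: 2.052 × 0.540 = 1.11.

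Pooling placebo alone shortens the interval by 1 − 1.11/1.68 = 34%. Pooling placebo and variance together shortens it by 1 − 1.11/2.00 = 45%.

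For an observed ratio of 1.75 to placebo:

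| Assumed SD of log change | Six v two (df 6) | Six v eight pooled (df 27) |
|---|---|---|
| 0.2 | +17% to +161% | +40% to +118% |
| 0.3 | −4% to +219% | +26% to +144% |
| 0.4 | −21% to +289% | +12% to +173% |
| 0.5 | −36% to +375% | +1% to +205% |

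**6. Gain from adjusting for V2.** Let ρ be the V2–V7 correlation on the log scale (assumed 0.5 to 0.8). Against unadjusted V7 levels, residual variance falls by ρ², which is 25% to 64%. Against a simple change from V2 it falls by 1 − (1 + ρ)/2, which is 25% at ρ = 0.5 and only 10% at ρ = 0.8.

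**The case against.** A reader might infer that the plan credits natural Treg recovery to the drug. The documents do not support that. Background says Tregs appear reduced in ACS but gives no recovery, rate or time course. A same-visit contrast between concurrent groups cancels a shared time trend. The bias arises only if the 75% is judged on active patients alone, which the endpoint wording allows but no section prescribes.

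Three other strong readings also fail:
- **That no baseline is used.** The endpoint is worded as a change, so a V2 reference is implied. What is missing is any use of V2 in the stated formal comparison.
- **That placebo is excluded.** The design is placebo-controlled, placebo could be meant as dose zero, and individual profiles and a dose-effect plot are planned as well.
- **That p values contradict the exploratory status.** The article disclaims only confirmatory testing, so exploratory p values are compatible with it.

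It is also fair to say that covariates, scale and pooling commonly sit in an SAP, which is not at hand, and that the log-scale remark concerns summaries in general. Their absence from a journal article is not counted as a fault here.

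What stands is narrower. The reference for a primary threshold belongs in the endpoint definition, and the comparison that the article does state is not matched to that endpoint.

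**Conclusion.** The point holds for part B as a mismatch between a primary endpoint and its stated analysis. The 75% target has no named comparator, and differences between doses at V2 and V7 do not show whether a dose meets it.

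The size of any bias cannot be derived from the documents. The 59%, 46% and 25% figures rest wholly on assumed placebo rises of 10%, 20% and 40%, and with flat placebo there is no bias. The 48% against 16% comparison depends on a scenario placed at the threshold, and with flat placebo it becomes 9% against 16%. It should not be quoted as a general error rate.

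The precision gain needs no assumed SD: 1.11 SD with pooled placebo, against 2.00 SD within a group or 1.68 SD at equal degrees of freedom. It does assume no drift in placebo across groups.

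This is a cheap improvement and does not invalidate the trial. In part A, where Treg is exploratory, it is a matter of consistent description only.

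**What to change.** For the part B primary Treg endpoint:
- Analyse log V7 Treg adjusted for log V2 Treg, with dose as a factor and the 8 part B placebo patients pooled as reference.
- Report each dose's ratio to placebo with 95% CI, beside the within-group change from V2.
- State which of these two the 75% target refers to.
- Enter placebo as dose 0 in the dose-effect plot, and drop the V2 comparison.

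Use the same model descriptively in part A. Reconcile Statistical methods and data handling, which lists Treg among the secondary biomarker endpoints, with Outcome measure, Part B, which makes it primary.

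The cost is wording in the protocol and SAP, with no new samples or patients. There are two downsides. Pooling placebo assumes no drift across successively enrolled groups, which a sensitivity analysis should examine. And some doses may fall short of 75% once compared with placebo.

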### Patient and public involvement

Heart attacks are distressing and impacts patients’ lives dramatically.^35^ The aim of this research is to help ameliorate this issue and potentially reduce reoccurrence. Lay members of the ethics committee reviewed this study and made constructive comments, which have been addressed. Patients were not involved in the recruitment to or conduct of the study. All patients provided full informed consent, with at least 24 hours to consider the information and at least two opportunities to discuss the trial in detail with the investigators. The results of the study will be disseminated to all study patients at the end of the trial.

### Study timeline

The trial began on the 15May 2017. The anticipated final follow-up visit(s) will be in January 2019. Primary analyses are projected to be completed by February 2019.
